### Patient recruitment

Generally, informed consent will be obtained by the investigators after personal elucidation from all participants prior to enrollment in the study. All patients presenting themselves in the outpatient clinic of our university hospital for the evaluation of symptoms indicating a stable CAD (e.g., exercise-related angina pectoris or dyspnea) will be screened prospectively. Patients at intermediate to high risk (according to recommended risk scores) and a class I or IIa indication for diagnostic coronary angiography (Additional file 4: Table S1) will be considered eligible unless they exhibit the following exclusion criteria: unstable angina pectoris, cardiac or respiratory instability, contraindication for CMR examination [17], known allergy to gadolinium-based contrast agents, impaired renal function (glomerular filtration rate <30 ml/min), contraindication or allergy to adenosine, pregnancy, age below18 years and inability to give written informed consent. It is irrelevant whether a CAD has already been diagnosed at the time of first presentation.

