### Protocol

All patients receive thorough history-taking, physical examination and a basic cardiological work-up including rest electrocardiogram, treadmill testing and echocardiography. Further prediagnostics (e.g., stress-echocardiography) is allowed and the respective results will be documented. According to general recommendations, risk stratification scores for each individual are calculated [18, 19]. In order to assess symptom burden and quality of life, the standardized Seattle Angina Questionnaire (SAQ) is carried out in each subject [20, 21]. All patients receive guideline-directed medical therapy (GDMT) [1].

Patients are randomized in two groups in a 1:1 fashion (blocked computer-generated random numbers). The allocation sequence is only available to a designated study nurse who will be phoned in case of an allocation. The trial is designed in an open-label fashion, i.e., there is no blinding after the initial allocation.

In group 1, patients directly undergo diagnostic coronary angiography. A PCI is performed according to current guidelines in case of ≥70% stenosis in a coronary vessel with ≥2-mm diameter [1, 2] or hemodynamically relevant stenoses in fractional flow reserve (FFR) testing.

Subjects in group 2 initially receive adenosine perfusion CMR for functional testing. The examination is conducted on a 3.0-Tesla whole-body scanner with a 32-channel phased-array cardiac receiver coil according to a well-established standard protocol [22–24]. In case reversible ischemia can be detected, subjects are sent to coronary angiography and PCI afterwards. Additional file 5: Figure S1 provides the study flowchart.

In case of progressive or insufficient symptom control, patients of group 2 (CMR group) are also evaluated for an invasive therapeutic approach. The following procedures will be documented.

There are no other diagnostic or therapeutic interventions planned or prohibited in the setting of this trial.

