### Sample size prediction/statistics

It has been shown that the annual event rate for the defined primary endpoint is 6.3% in case of a pathological and 1.0% in case of a normal CMR examination [27]. Retrospective analysis of our data revealed a 30% rate of pathological CMR examinations during the last years, thus the expected annual event rate would be 2.59% for the whole primary CMR group. In patients primarily undergoing coronary angiography, pooled annual event rates have been shown to be about 6% [6, 28]. For the sample size prediction, a Fisher’s exact test with a power of 80% and a *p* value indicating significance of < .05 was used. The study was designed to prove non-inferiority with a defined non-inferiority margin of 1% within a 3-year follow-up period. This lead to a predicted sample size of 90 participants per group. Taking dropout rate and safety margin into account, we plan to enroll 100 patients into each group. Annual interim analyses will be performed to evaluate the need for further enrollment in case of insufficient event rates for an appropriate statistical analysis.

The following statistical tests will be used after completion of follow-up: to test the relationship between categorical classification factors, the chi-squared test will be applied. Continuous variables will be tested for normal distribution by the D’Agostino-Pearson test. In case of a normal distribution, variables will be reported as mean ± standard deviation and a two-tailed *t* test will be applied for comparison. Variables without normal distribution will be reported as median with percentiles and the Mann-Whitney rank-sum test will be used for comparison. As mentioned above, Fisher’s exact test will be applied to test for non-inferiority of the event rates of both groups. Overall, a *p* value ≤ .05 will be judged significant.

Data management will only be carried out by trained personal. The database is stored on protected servers of the academic hospital.

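### Known versus suspected CAD is on record before allocation, but the primary comparison does not use it: a minor, cheap precision gain, not a design error or a bias

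*Protocol article*

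**What the plan says.** All places are in the protocol article, under Methods/design.

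- **Population.** The Background states the objective for patients with suspected or known CAD. Patient recruitment closes its eligibility paragraph with "It is irrelevant whether a CAD has already been diagnosed at the time of first presentation". The same paragraph restricts entry to "Patients at intermediate to high risk (according to recommended risk scores) and a class I or IIa indication for diagnostic coronary angiography".
- **Baseline information.** The Protocol section has a history and individual risk scores taken in every patient, and describes this before it describes randomisation.
- **Allocation.** "Patients are randomized in two groups in a 1:1 fashion (blocked computer-generated random numbers"). No stratification factor is named, and none is ruled out.
- **Primary comparison.** Sample size prediction/statistics names Fisher's exact test for the non-inferiority comparison of event rates, with no baseline factor. On the margin: "The study was designed to prove non-inferiority with a defined non-inferiority margin of 1% within a 3-year follow-up period". I read this as 1 percentage point on the 3-year risk difference.
- **Event rates.** "the annual event rate for the defined primary endpoint is 6.3% in case of a pathological and 1.0% in case of a normal CMR examination". For the angiography group, "pooled annual event rates have been shown to be about 6" per cent. The article gives no rate by CAD status.

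**The concern.** A patient with established CAD may well carry a different 3-year risk of cardiac death or infarction from one in whom CAD is only suspected. With 100 patients per group, the two groups will differ somewhat in their share of known CAD by chance. A crude 2x2 test leaves that variation in the estimate, while a stratified estimate takes most of it out. The information is already collected, so using it costs almost nothing.

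At stake is a slightly narrower confidence interval for the risk difference. The validity of the randomised comparison is not at stake.

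**Working it through.** **1. The plan's own figure.** With "Retrospective analysis of our data revealed a 30% rate of pathological CMR examinations" and the two annual rates quoted above, 0.30 x 6.3% + 0.70 x 1.0% = 1.89% + 0.70% = 2.59%. This agrees with "the expected annual event rate would be 2.59% for the whole primary CMR group".

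**2. Assumptions that the article does not supply.**
- Share of known CAD, f: 30% and 50%.
- 3-year risk gap D between known and suspected CAD. As an upper case I borrow the only prognostic split in the article, that by CMR result: 1 - (1 - 0.063)^3 = 17.7% and 1 - (1 - 0.010)^3 = 3.0%, so D = 14.8 points. As a lower case I take about half of that, 7 points, and then no gap at all. The CMR result is a proxy here. It is not evidence about CAD status.

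**3. Variance that stratification can remove.** With mean risk p, the between-stratum share of the variance is f(1 - f)D^2 / [p(1 - p)].

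| | f = 30% | f = 50% |
|---|---|---|
| p at D = 14.8 points | 0.3 x 17.7% + 0.7 x 3.0% = 7.4% | 0.5 x 17.7% + 0.5 x 3.0% = 10.4% |
| Share at D = 14.8 points | 0.21 x 0.0218 / 0.0685 = 6.7% | 0.25 x 0.0218 / 0.0928 = 5.9% |
| Share at D = 7 points, same p | 0.21 x 0.0049 / 0.0685 = 1.5% | 0.25 x 0.0049 / 0.0928 = 1.3% |

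**4. Price of stratifying.** With Mantel-Haenszel weights, two strata and N = 200, the variance rises by about 1/N = 0.5% when the factor is not prognostic. Simulation of the Mantel-Haenszel estimate agrees: a net gain of about 6% at D = 14.8 points, a net gain of about 1% at D = 7 points, and a loss of about 0.5% with no gap.

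**5. Effect on the interval.** The crude standard error with 100 per group is sqrt[2p(1 - p)/100], which is 3.7 points (f = 30%) or 4.3 points (f = 50%). Even in the upper case it falls by only 1 - sqrt(1 - 0.067), about 3%. The 95% half-width goes from about 7.3 to 7.0 points, or from about 8.4 to 8.2.

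At a higher mean risk the gain is smaller. With 18% (3 x 6%), f = 50% and D = 15 points, perfect balance lowers the simulated standard deviation of the difference from 5.49 to 5.38 points: 1 - (5.38/5.49)^2 = 4% of the variance.

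**6. Chance imbalance.** The standard deviation of the difference in known-CAD shares is sqrt[2f(1 - f)/100] = 6.5 points (f = 30%) or 7.1 points (f = 50%).
- An imbalance of 10 points or more, in either direction, has a chance of 12% or 16%.
- At D = 14.8 points, a 10-point imbalance shifts the risk difference by 0.10 x 14.8 = 1.5 points. A shift of at least 1 point needs an imbalance of 1/14.8 = 6.8 points, with a chance of 30% or 34%. About half of these shifts go against CMR.
- At half that gap, the chance of a 1-point shift is 4 to 6%.
- At D = 5 points, a shift above 1 point against CMR has a chance of about 0.1%.

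**7. Type I error without stratification.** With a true difference equal to the margin, 18% mean risk and D from 5 to 20 points, simulation gives a one-sided error of 2.6% against a nominal 2.5% at every gap. The imbalance is already part of the standard error.

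**The case against.** The strongest objection is that this is reviewer preference. The gain is a few per cent of the variance at best and could be slightly negative. Its size rests on a borrowed gap, and restricting entry by risk may narrow the true one. Other baseline factors, such as the risk scores calculated for every patient, could serve equally well. All of that stands, and it is why the point is minor. What remains is that the primary comparison is actually named, and it is a crude test although a plausible prognostic factor is on record.

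Three stronger readings are tempting, and the article does not support them.

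- *The plan treats CAD status as prognostically irrelevant.* The sentence concerns eligibility. It says that both kinds of patient may enter, which matches the stated objective.
- *Randomisation is unstratified.* The article names no factor, but it is a condensed account and the full protocol is not shown. Silence there is no finding.
- *A chance imbalance can decide the trial because it can move the difference by more than the margin.* The 30 to 34% chance of a 1-point shift counts both directions and depends on the borrowed gap. More importantly, such shifts are ordinary sampling error, and the test keeps its level. One event in 100 patients is also 1 point.

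**Conclusion.** The point holds as a minor suggestion. Stratifying the primary estimate by known versus suspected CAD would lower its variance by about 1% to 6-7%, and the standard error by at most about 3%, if 30 to 50% of patients have known CAD and the 3-year gap is 7 to 15 points. In a 200-patient trial that is worth about 2 patients (0.01 x 200) to 12-14 patients (0.06 to 0.07 x 200). If CAD status is not prognostic, the loss is about 0.5%, or one patient.

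Enrolling both kinds of patient is not an error, and the unstratified comparison is neither biased nor anticonservative on this account. The larger limitation is the 1-point margin against a standard error of about 4 to 5 points: under the planned linear 3-year rates of 18% and 3 x 2.59% = 7.77%, it is sqrt[(0.18 x 0.82 + 0.0777 x 0.9223)/100] = 4.7 points. Stratifying does not change that.

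**What to change.** - **Analysis, all patients.** Define known CAD from the baseline history (for example prior infarction, revascularisation or documented stenosis). Estimate the 3-year risk difference stratified by known versus suspected CAD, for example with Mantel-Haenszel weights, and compare its confidence limit with the 1-point margin. This also covers patients already randomised and gives a quantity that can be set directly against the margin.
- **Allocation, optional.** If it is not already stratified, use separate blocks by CAD status for the patients still to be enrolled; recruitment was ongoing at submission. Keep the stratified analysis in that case, since balanced allocation with a crude test does not bring the gain into the interval.
- **Timing.** Fix the definition and the estimator before any further comparison of outcomes by group, and record the change with the ethics committee and the registry, as the article provides for protocol modifications.

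The cost is one sentence of analysis text and, if the option is taken, a second list for the study nurse who already holds the sequence. No extra patients or data are needed.

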### Protocol

All patients receive thorough history-taking, physical examination and a basic cardiological work-up including rest electrocardiogram, treadmill testing and echocardiography. Further prediagnostics (e.g., stress-echocardiography) is allowed and the respective results will be documented. According to general recommendations, risk stratification scores for each individual are calculated [18, 19]. In order to assess symptom burden and quality of life, the standardized Seattle Angina Questionnaire (SAQ) is carried out in each subject [20, 21]. All patients receive guideline-directed medical therapy (GDMT) [1].

Patients are randomized in two groups in a 1:1 fashion (blocked computer-generated random numbers). The allocation sequence is only available to a designated study nurse who will be phoned in case of an allocation. The trial is designed in an open-label fashion, i.e., there is no blinding after the initial allocation.

In group 1, patients directly undergo diagnostic coronary angiography. A PCI is performed according to current guidelines in case of ≥70% stenosis in a coronary vessel with ≥2-mm diameter [1, 2] or hemodynamically relevant stenoses in fractional flow reserve (FFR) testing.

Subjects in group 2 initially receive adenosine perfusion CMR for functional testing. The examination is conducted on a 3.0-Tesla whole-body scanner with a 32-channel phased-array cardiac receiver coil according to a well-established standard protocol [22–24]. In case reversible ischemia can be detected, subjects are sent to coronary angiography and PCI afterwards. Additional file 5: Figure S1 provides the study flowchart.

In case of progressive or insufficient symptom control, patients of group 2 (CMR group) are also evaluated for an invasive therapeutic approach. The following procedures will be documented.

There are no other diagnostic or therapeutic interventions planned or prohibited in the setting of this trial.

### Follow-up

Adherence will be achieved by regular contact between the study personal and the participants. Follow-up information is gathered on a yearly basis after enrollment by outpatient clinic visits and by telephone interviews of patients and their general practitioners. Any reported adverse event will be reported and its significance evaluated by the investigators. At this time point, interim analyses will be performed by the investigators. The study will be stopped by the investigators if a safety concern arises that prohibits the continuation of the trial.

The primary endpoint is defined as cardiac death (defined as in [25]) and non-fatal myocardial infarction according to the current universal definition [26]. Any diagnostic or interventional coronary procedure that has not been scheduled at the time of the initial diagnostic work-up will be recorded as an unplanned procedure. Symptom burden and quality of life are assessed by SAQ each year. A follow-up period of 3 years is planned for each patient. Standardized follow-up forms have been established and are available at our institution. If consent is withdrawn by a participant, the data that has already been collected will be removed from further analysis.

Figure 1 shows the study schedule according to the populated SPIRIT figure.

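### Removing data already collected when consent is withdrawn can take randomised patients and recorded non-fatal events out of an open-label non-inferiority comparison

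*Protocol article*

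**What the plan says.** The rule is in the protocol article, Follow-up: "If consent is withdrawn by a participant, the data that has already been collected will be removed from further analysis". It is not limited to data that would arise after withdrawal, nor to participants who ask for erasure. Nothing else in the article keeps such a participant, or an event already recorded, in the analysis.

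Three other statements bear on it:

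- Protocol section: "Patients are randomized in two groups in a 1:1 fashion", and "there is no blinding after the initial allocation".
- Follow-up section: the primary endpoint is cardiac death and non-fatal myocardial infarction. Unplanned coronary procedures and the SAQ are also recorded over 3 years.
- Sample size prediction/statistics: the trial has a "defined non-inferiority margin of 1% within a 3-year follow-up period". On size, "This lead to a predicted sample size of 90 participants per group", and "Taking dropout rate and safety margin into account, we plan to enroll 100 patients into each group".

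**The concern.** The rule lets a decision taken after randomisation determine who is analysed. Participants know their group, so the decision to withdraw may depend on the strategy received and on what happened under it. Where it depends on both, the remaining patients are no longer the groups that were randomised.

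This matters more than usual for two reasons. In a non-inferiority trial, losing events from the new strategy makes it look acceptable. And with about 100 patients per group and a margin of 1%, very few events separate success from failure. The ten extra patients per group replace numbers; they do not restore a deleted infarction.

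**Working it through.** **Inputs from the protocol article.** Annual event rates: "the expected annual event rate would be 2.59% for the whole primary CMR group", and for angiography "pooled annual event rates have been shown to be about 6" per cent. The CMR figure reproduces: 0.30 × 6.3% + 0.70 × 1.0% = 2.59%. Over 3 years, by simple multiplication, this is 3 × 2.59% = 7.77% for CMR and 3 × 6% = 18% for angiography, or about 8 and 18 events per 100. The margin is read as 1 absolute percentage point on the 3-year rate. The article does not spell this out.

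**Step 1: effect of one deletion.** The patient leaves numerator and denominator, so the shift is e/n − (e − 1)/(n − 1).

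| Group | n | Before | After | Shift (points) |
|---|---|---|---|---|
| CMR | 100 | 8/100 = 8.00% | 7/99 = 7.07% | 0.93 |
| Angiography | 100 | 18/100 = 18.00% | 17/99 = 17.17% | 0.83 |
| CMR | 90 | 7/90 = 7.78% | 6/89 = 6.74% | 1.04 |
| Angiography | 90 | 16/90 = 17.78% | 15/89 = 16.85% | 0.92 |

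Deleting an event-free patient at n = 100 raises the rate by only 0.08 points (CMR, 8/99 − 8/100) or 0.18 points (angiography, 18/99 − 18/100).

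**Step 2: can one deletion change the verdict?** Take the difference d = CMR − angiography and the one-sided 95% upper bound d + 1.645 × SE, with SE = √[p₁(1 − p₁)/n₁ + p₂(1 − p₂)/n₂]. Non-inferiority requires a bound below +1 point.

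- 11/100 against 18/100: d = −7.00, SE = 4.95, bound +1.15 points. It fails.
- One CMR event patient deleted, 10/99 against 18/100: d = −7.90, SE = 4.89, bound +0.15 points. It passes.
- Planned rates, 8/100 against 18/100: SE = 4.70, bound −2.3 points. After one CMR deletion, 7/99 against 18/100: bound −3.3 points. It passes both times.

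So one deletion matters only near the boundary.

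**Step 3: error rate under assumed withdrawal.** The article gives no withdrawal rate, so every rate below is an assumption. The set-up is also assumed: true 3-year rates exactly at the margin (12% angiography, 13% CMR), 100 per group, and the unpooled bound of Step 2 at one-sided .05, because the sidedness of the planned test is not stated. Results are from simulations of at least 400,000 trials.

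| Withdrawn and deleted | False non-inferiority |
|---|---|
| Nobody | about 5.3% |
| 8% of everyone, unrelated to outcome | 5.2% |
| 20% of event patients and 8% of others, same in both groups | 5.5% |
| 20% of angiography event patients, 8% of all others | 2.8% |
| 10% of CMR event patients, 5% of all others | 6.7% |
| 20% of CMR event patients, 8% of all others | 9.6% |
| 30% of CMR event patients, 6% of other CMR patients, 8% of angiography patients | about 16% |

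The mean observed difference, truly +1.0 point, becomes −0.5 in the 9.6% case and −2.0 in the 16% case. In the 9.6% case the average number of events deleted is 13 × 0.20 = 2.6 in the CMR group and 12 × 0.08 ≈ 1.0 in the angiography group.

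**Step 4: fatal events.** A participant who has died cannot withdraw, so only non-fatal infarctions are exposed. If half of events are fatal (assumed; the split is not given), the last two rows fall to about 7% and about 10%.

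**The case against.** The strongest reply is that the harm is conditional. Withdrawal unrelated to outcome does nothing to the error rate, and outcome-related withdrawal that is equal in both groups does almost nothing. Inflation needs CMR patients with events to withdraw distinctly more often than other CMR patients, with no matching pattern in the angiography group. The article offers no evidence for that asymmetry. This stands, and it limits the size of the finding.

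Four stronger readings are tempting and are not supported:

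- *The bias runs towards non-inferiority.* An angiography patient with an infarction may equally withdraw, which biases the other way (2.8% in Step 3). CMR patients with ischaemia are sent to angiography, and those with insufficient symptom control are evaluated for an invasive approach, so particular dissatisfaction in that group is conjecture.
- *One lost event equals the margin.* The net shift at n = 100 is 0.83 to 0.93 points. If 1% means per year (3 points over 3 years), one event is about a third of the margin.
- *The plan expects ten deletions per group.* The ten extra patients cover dropout and a safety margin together, without a split, and a patient lost to follow-up is not covered by the deletion rule.
- *The error rate is 10–16%.* That is one end of a range produced by assumptions.

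The consent form is not shown, and the rule may carry out a promise made there. That bears on patients already enrolled, and the fix allows for it. None of this is a reason to keep the rule as it stands: it is explicit, and it leaves the validity of the comparison resting on withdrawal not depending jointly on group and outcome.

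**Conclusion.** The concern holds in a limited form and should be fixed. As written, the rule permits randomised patients and their recorded non-fatal primary events, unplanned procedures and SAQ scores to be removed after allocation in an open-label trial. If withdrawal depends on both group and outcome, the comparison is biased, in a direction that cannot be known in advance.

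On the literal margin, one deleted event patient is worth about 0.8 to 1.0 point against 1 point, but the standard error at the planned rates is about 4.7 points, so a single deletion decides the result only near the boundary. Across the assumed withdrawal patterns, the nominal 5% error runs from about 3% to about 16%, the upper end falling to about 10% if half of events are fatal. These figures rest on assumed withdrawal rates, true rates of 12% and 13%, and a one-sided .05 test of the difference; the article supplies none of these. The documents do not support a claim that the trial's error rate is inflated, only that the rule leaves it unprotected.

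**What to change.** Replace the sentence in the Follow-up section with: *After withdrawal of consent no new data are collected; data recorded before withdrawal are kept and analysed in the randomised group, unless the participant expressly requests erasure or the consent already signed requires it.*

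In addition:

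- Count events recorded before withdrawal in the primary comparison. Simply censoring at withdrawal would not do, because the planned Fisher's exact test works on event counts.
- Report withdrawals and erasures by group.
- Add a sensitivity analysis over a range of assumed event rates for withdrawn or erased patients, applied to both groups. Counting only erased CMR patients as events would be a one-sided extreme: eight such patients would add about 8 points against a 1-point margin.

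The cost is a small amendment to the protocol and consent form with notice to the ethics committee. Recruitment was ongoing at submission, so later participants can enter under the new wording. Those already enrolled stay under the consent they signed, so some deletions may remain, and the reporting and sensitivity analysis should cover them.
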